### 3.3 Run-In phase with insulin pump training

Patients who have signed an informed consent statement, met the eligibility criteria, have successfully demonstrated proficiency with using the iPro CGM, and performed self monitoring blood glucose (SMBG) at least 4 times daily during the iPro training period (up to 8 weeks) will continue into the run-in

phase in which they will learn to operate the insulin pump coupled with the MiniLink™ REAL-Time Transmitter Continuous Glucose Monitoring System (RT-CGMS). At the end of the run-in phase, patients must show competency with operating the insulin pump and RT-CGM to be eligible for participation in the GLUMIT-DG study. Specifically, the patient must be able to check interstitial glucose levels with the RT-CGM as well as blood glucose with the traditional finger stick method (SMBG) at least 4 times daily using a glucose meter. In addition, patients must be able to manage the insulin pump, which includes adjusting insulin dosing according to standards provided by the GLUMIT-DG study physician and diabetes educator. Patients must also be able to electronically transfer data from the RT-CGM via their home computer to the GLUMIT-DG study staff. Both the diabetes educator and the diabetologist will assist in patient troubleshooting of the RT-CGM during the run-in period and for the duration of the study. After successful completion of the run-in phase, patients will be enrolled into the GLUMIT-DG study for 24 weeks for control of glycemia using the RT-CGM as an adjunct to SMBG measurements to guide insulin pump treatment. The initial insulin pump parameters will be set as follows:

**For those patients who were not using an insulin pump prior to screening,** parameters will be set initially based on type of diabetes and body weight (BW in kilograms)

**For Type 2 diabetes:**

1. Initial hourly basal insulin rate will be estimated as  $(BW \times 0.4)/24$  units of insulin
2. The initial carbohydrate to insulin ratio for meal boluses will be estimated as  $450/(BW \times 0.84)$  (grams of carbohydrate per unit insulin)
3. Initial correction factor for fasting glycemia  $>110$  mg/dL, postprandial  $>140$  mg/dL will be estimated as  $1700/(BW \times 0.8)$  for capillary glucose drop per unit insulin

**For Type 1 diabetes:**

1. Initial hourly basal rates will be estimated as  $(BW \times 0.2)/24$  units of insulin
2. Initial meal boluses using a carbohydrate to insulin ratio will be estimated as  $450/(BW \times 0.2)$  (grams of carbohydrate per unit insulin)
3. Initial correction factor for fasting glucose  $>110$  mg/dL, postprandial  $>140$  mg/dL will be estimated as  $1400/(BW \times 0.4)$  for capillary glucose drop per unit insulin

Alternatively, for those patients who are using a Basal-Bolus approach to control their Type 1 diabetes, the insulin pump may be programmed to use their current basal dose and carbohydrate to insulin ratios as well as correction factor.

**For those patients who are already on insulin pumps,** the insulin parameters will be adjusted based on the best prediction of needs using results from both finger stick data and baseline (run-in period) RT-CGM data.

Overall the targets for glycemia management will be:

1. Fasting glucose: 80-120 mg/dL
2. Postprandial excursions: 100-180 mg/dL

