#### 5.4 Run-in visits with insulin pump training

After successful completion of iPro (or iPro2) training, patients will return for four weekly visits, for a minimum of two weeks up to an 8-week learning period to receive training on the usage of an insulin pump coupled with RT-CGM. Participants will be trained on how to use a computer to send the data gathered by the RT-CGM, glucose meter and insulin pump to their study physician and diabetes educator. During the run-in period insulin pump infusion parameters will be adjusted to optimize regulation of blood glucose levels, using information from both their SMBG and from trend analysis of the RT-CGM which will be used only as an adjunct to SMBG.

**Run-in visit 1:** Participants will receive instruction on use of the RT-CGM, including the uploading of the data using the CareLink system as well as instructions on glycemia management using their SMBG which will be supplemented with the trend identification using the RT-CGM. The RT-CGM has a feature known as “REAL-Time Alarms” which will be set to warn patients when their glucose levels are very low or very high. The hypoglycemic alarm threshold will be set at 80 mg/dL and the hyperglycemic alarm threshold will be set at 240 mg/dL. The low glucose snooze will be set between 15-20 minutes to allow time to observe the effect of treatment for the hypoglycemia, and the high glucose snooze will be set to 1-2 hours to allow time to observe the effects of a corrective dose of insulin. They will be taught how to calibrate their RT-CGM using 2-4 glucose readings each day, obtained when there is a low rate of glucose change, as indicated by an absence of rate of change arrows. The subjects will be instructed to not make any insulin dose decisions based on the RT-CGM glucose reading without obtaining a blood glucose measurement using their glucose meter. Insulin doses may be modified based on the glucose rate of change, as was done during the JDRF and STAR 1 and STAR 3 trials. (See package insert for instructions for use of CGM)

**Run-in visit 2:** This visit should be planned within a week after the first run-in visit. Patients will be taught insulin infusion pump mechanics and will be started on an insulin pump filled with saline. The purpose of filling the pump with saline is to ensure that the patient can tolerate wearing it before it is filled with insulin.

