**Run-in visit 3:** Patients will stop previous diabetes treatment and insulin administration with the pump will be initiated according to predetermined insulin dose parameters. For those patients who entered the study using an insulin pump, parameters will be adjusted as per their meter blood glucose readings using their RT-CGM readings as adjunctive information. Carbohydrate to insulin ratios, insulin sensitivity, insulin on board (3 to 5 hours), and glycemic targets will be established by the study staff. Patients will be instructed to only use the bolus wizard feature of the pump when delivering insulin doses for meals to ensure the proper amount of insulin is delivered. Due to the presence of gastroparesis, meal boluses for control of postprandial hyperglycemia combination meal boluses using a standard bolus and square wave bolus may be utilized with adjustments made based on post prandial glucose trends. This approach is aimed at minimizing a mismatch in insulin bolus administration and nutrient absorption due to delayed and possibly erratic gastric emptying. In addition to intensive education on glycemic control, participants will be instructed in depth on symptoms and signs of hypoglycemia and steps to correct it without caloric over replacement to avoid rebound hyperglycemia.

**Run-in visit 4:** Patients will review their RT- CGM results and receive additional education on glycemia management. They will also be taught how to use glucose trends as displayed by the RT-CGM as adjunctive information to their SMBG to modify their insulin doses and to ingest carbohydrates if the RT-CGM identifies a risk of hypoglycemia, if it is confirmed by a meter glucose reading. In addition, blood will be drawn to measure their hemoglobin A1c level.

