#### Meal Boluses

The adjustment for meal related glycemia is of special interest in the GLUMIT-DG study since gastric emptying may be erratic and delayed. For the GLUMIT-DG study, the following guidelines will be used for adjustment of meal boluses at all subsequent follow-up visits or phone contacts.

Insulin administered for meal(s) will be tailored using a dual wave pattern. The amount of insulin for the specific meal will be estimated using the carbohydrate to insulin ratio (CHO:I). This ratio is the estimated amount of meal carbohydrate that one unit of insulin metabolizes. This ratio is calculated initially by the following formulas (see also Section 3.3):

(1)  $450/(\text{BW (kg)} \times 0.84)$  for Type 2 diabetes, and

(2)  $450/(\text{BW (kg)})$  for Type 1 diabetes

The carbohydrate to insulin ratio is in the following units: grams of meal carbohydrate for every unit of insulin. The ratio is entered into the insulin pump. When the patient is about to eat or has already eaten, he/she enters into the pump the estimated amount of carbohydrate ingested during the meal or the meal the patient is preparing to eat. The microchip in the pump uses the pre-entered CHO:I ratio to calculate the bolus of insulin to be delivered. For example, if the meal carbohydrate is calculated as 90 grams and the CHO:I ratio is 30, then the pump will calculate a total of 3 units of insulin. If the same amount of meal carbohydrate is eaten and the CHO:I ratio is 10, then the total amount of meal insulin calculated is 9 units. Thus a higher CHO:I ratio yields a lower calculated insulin bolus and vice versa. The pump will prompt the user to confirm acceptance of the suggested dose and will not deliver the bolus unless the patient accepts the suggestion from the pump.

The bolus of insulin can be delivered in TOTAL during a short period of time (standard bolus) or it can be

delivered over a prolonged period of time (extended or square wave bolus). A dual wave bolus can be configured by delivering a certain % of the dose immediately (standard bolus) and the rest over several hours after meal ingestion (extended square wave bolus). These times can be tailored as per the judgment of the diabetologist and diabetes educator. For obvious reasons, the second approach is better suited for patients with gastroparesis since it diminishes the possibility of hypoglycemia and will be used in the GLUMIT-DG study.

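### Sections 3.3 and 5.7 print starting carbohydrate-to-insulin ratios for type 1 diabetes that differ five-fold, and the protocol does not show which is intended

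*Protocol*

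**What the plan says.** Section 3.3 lists the initial pump settings. It introduces the formulas with "For those patients who were not using an insulin pump prior to screening" and gives body weight (BW) in kilograms.

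- **Type 2, Section 3.3:** "The initial carbohydrate to insulin ratio for meal boluses will be estimated as" 450/(BW × 0.84), in grams of carbohydrate per unit of insulin.
- **Type 1, Section 3.3:** "Initial meal boluses using a carbohydrate to insulin ratio will be estimated as" 450/(BW × 0.2), in the same units.
- **Exception, Section 3.3:** for type 1 patients already on a basal-bolus regimen, "the insulin pump may be programmed to use their current basal dose and carbohydrate to insulin ratios as well as correction factor".

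Section 5.7 (Meal Boluses) returns to the same quantity: "This ratio is calculated initially by the following formulas (see also Section 3.3"). It then prints 450/(BW × 0.84) for type 2 and 450/BW for type 1, again with BW in kg and the ratio in grams per unit.

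The formulas come into use at run-in visit 3 (Section 5.4), when previous treatment stops and "insulin administration with the pump will be initiated according to predetermined insulin dose parameters".

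**The concern.** Both sections claim to give the initial type 1 ratio, and 5.7 cites 3.3 as its companion. The type 2 formula is the same in both places, so the sections were evidently meant to agree. The type 1 formulas do not, and no other text reconciles them.

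The ratio is entered in the pump and divides into the meal carbohydrate to produce the suggested bolus. Too low a ratio inflates every suggested meal bolus; too high a ratio under-doses every meal. In a study whose primary outcome is hypoglycemia, and which classes severe hypoglycemia as a serious adverse event (Section 7.1), the starting insulin rule should have one value.

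**Working it through.** **The protocol's own example.** Section 5.7 computes bolus = carbohydrate ÷ ratio: 90/30 = 3 units and 90/10 = 9 units. Both reproduce.

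**Inputs.** Type 1 ratio 450/(BW × 0.2) from Section 3.3 and 450/BW from Section 5.7. The 90 g meal is the one in the 5.7 example. Body weights are assumed.

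**Ratio of the two formulas.** [450/(BW × 0.2)] ÷ [450/BW] = 1/0.2 = 5.0. Body weight cancels, so the gap is five-fold for every patient.

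| Assumed weight | 3.3 ratio (g/unit) | 5.7 ratio (g/unit) | 90 g bolus, 3.3 (units) | 90 g bolus, 5.7 (units) |
|---|---|---|---|---|
| 50 kg | 45.0 | 9.0 | 2.0 | 10.0 |
| 70 kg | 32.1 | 6.4 | 2.8 | 14.0 |
| 100 kg | 22.5 | 4.5 | 4.0 | 20.0 |

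These are pump suggestions, not predicted glucose effects.

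**A yardstick within the protocol.** Under 5.7, 90 g calls for 90 × BW/450 = 0.2 × BW units. Section 3.3 sets the type 1 basal rate at (BW × 0.2)/24 per hour, which is 0.2 × BW units over 24 hours. One 90 g bolus under 5.7 therefore equals a full day of starting basal insulin, at any weight.

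**Direction of error.**
- If 450/BW was intended and 3.3 is followed, meal insulin is 0.2 times the intended dose.
- If 450/(BW × 0.2) was intended and 5.7 is followed, it is 5.0 times the intended dose.

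**Would titration close the gap?** The largest step in the 5.7 table changes the ratio by 2 g per unit. At 70 kg the gap is 32.1 − 6.4 = 25.7 g per unit, and 25.7/2 is about 13 maximal steps. The table entries are suggestions, so clinicians may move faster, but the written algorithm alone would correct a wrong start slowly.

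**The case against.** **Section 3.3 governs.** It is the section that sets the initial parameters; 5.7 concerns later adjustment and only recaps the formula. If staff follow 3.3, neither printed formula makes the start an overdose. This stands, and it limits the hypoglycemia risk to sites that start from 5.7. It does not remove the conflict, because 5.7 also presents its formula as the initial calculation.

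**There are safeguards.** Of the settings at visit 3, which include the carbohydrate ratio, Section 5.4 says "glycemic targets will be established by the study staff". It adds: "During the run-in period insulin pump infusion parameters will be adjusted to optimize regulation of blood glucose levels". The sensor's low alarm is set at 80 mg/dL, boluses may be split or delayed, and the patient must accept each one. For under-dosing there are correction boluses and, in type 1, ketone testing (Section 6.3). These reduce the risk. But the staff setting the ratio are the readers given two values, and the patient accepts a number computed from whichever was entered.

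**The link to the primary outcome is indirect.** Formula starts occur in run-in, before the 24-week on-treatment count begins. A reader might infer that the conflict biases the primary result. The protocol does not show a starting value carrying into that period after run-in adjustment. A wrong start could affect the baseline rate if run-in weeks count as baseline, but that is an inference. The sample size calculation is unaffected.

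**A multiplier may have been lost.** The brackets around a single term in 5.7 could hint at this, in the source or in text conversion. It cannot be excluded, though the adjacent type 2 formula kept its 0.84.

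**Conclusion.** The contradiction is real and exact: a five-fold difference in a starting insulin rule, independent of weight. It should be fixed before any further formula-based type 1 start. The unit figures rest on the assumed weights; the factor of five does not.

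Several stronger readings are tempting but unsupported:

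- **That 5.7 is the wrong formula, so patients are being overdosed.** At 70 kg, 5.7 gives type 1 patients more for 90 g than the type 2 formula (14.0 against 90 × 70 × 0.84/450 = 11.8 units). That may look odd, but it does not establish intent.
- **That the intended multiplier is about 0.4.** In Section 3.3 the type 1 basal and correction multipliers (0.2 and 0.4) are half those for type 2 (0.4 and 0.8), which invites halving 0.84 as well. But the type 2 ratio and correction multipliers differ from each other (0.84 and 0.8), and the correction constants differ by type (1700 and 1400), so no common pattern is established.
- **That at most 20 patients are exposed.** Twenty is the type 1 enrollment target. Pump insulin starts at run-in visit 3, before enrollment, so patients who later fail run-in are also exposed.

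Three lesser points belong in the same amendment but do not carry the severity:

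- The titration table covers 15 of 4 × 4 = 16 combinations. A 1-hour value of 80–180 with a 3-hour value below 80 mg/dL has no row, although the explanatory text gives the general direction for low values.
- The satiety-test bolus (Sections 5.3 and 5.6) is written per 15 g of Ensure, whereas meal ratios are per gram of carbohydrate. A reader might infer a several-fold overdose, but sizing it needs a density and a carbohydrate content that the protocol does not give. Section 6.4 also delays these boluses until the sensor shows glucose rising.
- In Section 5.3, screening visit 2 treats glucose above 270 mg/dL and then proceeds to testing, while the EGG paragraph requires postponement to another day. The visit text does not say testing follows on the same day, so this needs only aligned wording.

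**What to change.** 1. Before any further formula-based type 1 pump start, the study diabetologists confirm the intended multiplier. No value is proposed here.
2. An amendment and a site memo state the confirmed formula identically in Sections 3.3 and 5.7.
3. Check the starting ratios of all type 1 patients started by formula, including those who failed run-in. Section 8.2 says pump data are uploaded and stored, but not that the programmed run-in ratio is among them, so clinic records may be needed.
4. In the same amendment: add the missing titration row, with its content decided by the diabetologists; confirm whether the satiety-test bolus is meant per 15 g of carbohydrate and, if so, say so in Sections 5.3 and 5.6; align the screening visit 2 text with the postponement rule.

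The cost is one amendment, one memo and one record look-up per affected patient. The number of look-ups cannot be read from the protocol.

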**3.4 Standard treatment recommendations**

During the screening and run-in period that may span up to 16 weeks prior to enrollment into the GLUMIT-DG study, patients will receive a standardized set of recommendations to manage their gastroparesis symptoms including dietary modification, weight loss if needed, and exercise. In addition to dietary modification, patients may use antiemetic, prokinetic, or pain medications as appropriate for their gastroparesis symptom management. These recommendations have been prepared by the GpCRC

---

Steering Committee as standard of care in the management of patients with diabetic gastroparesis (see Standard Operating Procedures IV: Standard of Care for Patients with Diabetic Gastroparesis). This will help ensure that patients receive standard of care treatment for gastroparesis.

---

## 4. Patient Selection

---

### 4.1 Recruitment

Forty patients will be recruited from the seven clinical sites of the GpCRC (approximately 10 patients from Wake Forest University and 5 patients per the remaining clinical centers) over a 12-month period:

- California Pacific Medical Center, San Francisco, CA (PI: [name])
- Stanford University, Palo Alto, CA (PI: [name])
- Temple University, Philadelphia, PA (PI: [name])
- Texas Tech University, El Paso, TX (PI: [name])
- University of Michigan, Ann Arbor, MI (PI: [name])
- University of Mississippi, Jackson, MS (PI: [name])
- Wake Forest University, Winston-Salem, NC (PI: [name])

The study will be implemented in two lead clinics (Wake Forest University and the University of Michigan) followed by the 5 additional clinical sites.

Patients with diabetic gastroparesis will be identified and registered for screening, iPro-CGM training, and the run-in period at the clinical centers subject to the inclusion and exclusion criteria listed below. Eligible patients will be enrolled after completion of all required study procedures including successful learning of RT-CGM as an adjunct to self monitoring blood glucose to guide insulin pump therapy, keying of all required data elements, and passing protocol eligibility checks for the GLUMIT-DG study. Patients may be recruited directly into the GLUMIT-DG study or may be recruited from other GpCRC studies.

Each clinical center will develop a recruitment plan. These plans will vary from clinic to clinic depending on the available pools of patients with diabetic gastroparesis and local recruitment resources. Clinics will attempt to recruit sufficient numbers of minorities and males.

### 4.2 Inclusion criteria

Patients with mild to moderate symptoms of diabetic gastroparesis will be studied. Patients should not have idiopathic or post-surgical gastroparesis etiologies and must satisfy the following inclusion criteria:

1. Age 18 – 70 years old at registration
2. Type 1 or type 2 diabetes mellitus for at least 2 years
3. Symptoms of gastroparesis (nausea, vomiting, early satiety, bloating fullness, discomfort) for at least 1 year prior to registration with a Gastroparesis Cardinal Symptom Index (GCSI) score of  $\geq 18$
4. Delayed gastric emptying on gastric emptying scintigraphy within 1 year of registration, defined as greater than 60% retention at 2 hours or greater than 10% retention at 4 hours
5. Hemoglobin A1c of at least 8.0% at registration with current therapy (insulin and/or oral hypoglycemic agents). This level of HbA1c indicates the need to advance treatment and makes the patient a candidate for insulin treatment (for those using oral agents only) or optimization of insulin therapy. Individuals already receiving diabetes therapy via an insulin pump will be eligible for participation if, in the opinion of investigators, he/she may acquire additional benefit from RT-CGM that might improve glycemic control
6. Normal upper endoscopy within 1 year of registration
7. No clinical or imaging evidence of obstruction
8. Successful use of the RT-CGM during the screening period
9. Access to a computer running Windows and with internet capabilities

### 4.3 Exclusion criteria

Patients who satisfy any of the following exclusion criteria will be ineligible for enrollment in the study:

1. Prior gastric surgery including fundoplication
2. Other systemic diseases potentially causative of gastrointestinal symptoms
3. Acute or chronic renal insufficiency with creatinine >1.5 mg/dL
4. Current psychiatric disease or eating disorder
5. Pregnancy
6. Any other condition which in the opinion of the investigators would impede compliance or hinder completion of the study

#### **4.4 Run-in phase**

Prior to enrollment into the GLUMIT-DG study, patients will undergo up to 8 weeks of a run-in phase in which they will learn to operate an insulin pump coupled with the MiniLink™ REAL-Time Transmitter Continuous Glucose Monitoring System (RT-CGM). At the end of the run-in phase, patients must show competency with operating the insulin pump and RT-CGM to be eligible for participation in the GLUMIT-DG study. Specifically, a patient must be able to check blood glucose levels with the RT-CGM as well as with the traditional finger stick method at least 4 times daily. In addition, patients must be able to manage the insulin pump which includes adjusting insulin dosing according to standards provided by the GLUMIT-DG study physician and diabetes educator. Patients must also be able to electronically transfer data from the RT-CGM via their home computer to the GLUMIT-DG study staff. Once a patient has shown the ability to complete all of these tasks and has confirmed their consent to participate, they may enroll into the GLUMIT-DG study.

---

